Sensory screening is also conducted in the eHealtHeart main modules. A vision test that follows the Snellen test guidelines will be available. The patient must keep the mobile phone screen at a certain distance and, by closing each eye, must assess the letters that the mobile app shows. At the end, an overall score is provided based on the patient’s answers. The Snellen test can be repeated as many times as the patient wants within a day. A hearing test that follows the whisper test guidelines will also be available. The procedure will play back certain sounds from the left to the right side of the smartphone speakers. On the basis of what the patient heard and did not hear, an overall score with scaling is provided. The whisper test can be repeated as many times as the patient wants within a day.

The eHealtHeart main modules also promote the management of geriatric syndromes. In the Incontinence Management module, a patient will be able to report urination incidents, follow instructions to exercise the pelvic muscles, and add reminders regarding pelvic floor exercises. The urination data will be stored on the CARDIOCARE server and will be available to the patient and the patient’s assigned health care professional. Furthermore, the patient will be prompted to exercise their pelvic floor muscles with the help of instructions and visual aids. The pelvic floor exercises have different difficulty levels (regarding, eg, repetitions and time).

A fall detection and fall prevention module will be available on the app. The system, using sensors from the mobile device, will try to detect whether the patient had a fall incident and will inform the caregiver to communicate with the patient. Furthermore, educational material containing guidelines and videos for fall prevention will be available to the patients.

On the first day of recruitment, each patient receives a mobile phone (with the CARDIOCARE app), a smartwatch, and a belt from their clinical center to be used during the first 6 months of the study. Details on the frequency and duration of the interventions are provided in Table 1.

**Table 1 table1:** Frequency of the interventions of the eHealtHeart mobile app.

Module and interventions		Frequency

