**Sensory screening**		
	Vision test Hearing test	At baseline and at month 6

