Secondary end points also include the cost-effectiveness of provided health care pathways, determined through costs combined with quality-adjusted life years (QALYs). Costs will consider health care provided, numbers of admissions and days spent in hospital, and patient costs for out-of-pocket expenses associated with their condition (ie, travel expenses [of both the patient and caregiver], over-the-counter medicines and supplements, complementary therapies not supported by the health care system, home help, and time away from work).

Psychological and behavioral variables will also be measured as secondary end points. Intrinsic (mental and physical) capacity will be evaluated through the comprehensive geriatric assessment using standardized patient-reported outcome measures where applicable, sensors and wearables, and performance tests. More specifically, the following variables will be measured—(1) mobility and locomotion (distance, balance, and gait speed), (2) sensory ability (Snellen test and whisper test), and (3) vitality status (exercise, electrocardiogram, HR variability, grip strength, nutritional or energy state, sleep, and fatigue)—together with a complementary frailty screening (using the Geriatric 8 frailty screening tool, declared as the preferred tool by the International Society of Geriatric Oncology for identifying frailty in older patients with cancer, including patients with breast cancer) and frailty assessment (comorbidity, mental health, cognition, functional status, polypharmacy, geriatric syndromes, and socioeconomic and nutritional status). Other psychological and behavioral variables measured are psychocognitive status (personal traits, cognitive factors, and emotional states), social and socioeconomic factors, and general QoL, measured using standardized validated questionnaires to make comparisons with the more specific psychological and behavioral measures listed previously.

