### Study Time Points and Procedures

After the patient has signed the written informed consent form, she will follow the study procedures set for each time point, as shown in Table 2. Table 3 shows all self-administered scales that the patient has to complete for each study time point. These procedures are the same for both the standard practice and enhanced monitoring groups.

**Table 2 table2:** Summary of scheduled procedures.

Procedure	Day −15: T0 (screening)^a^	T1 (baseline)^a^	Day 0: treatment start	Month 3: T2	Month 6: T3	Month 9: T4	Month 12: T5	14-25 days after the end of treatment^b^
ICF^c^ signature	✓							
Diagnosis	✓							
Personal and family medical history (including diagnosis of severe psychiatric disorders)	✓							
Smoking habits		✓						✓
Comorbidities	✓							
Oncological visit		✓			✓		✓	
Psychological visit^d^ (if the center has a psychological support service)		✓		✓	✓	✓^e^	✓	
Cardiological visit (if needed)	✓	✓		✓	✓	✓^e^	✓	
BP^f^ and HR^g^ measurement		✓		✓	✓	✓^e^	✓	
Routine blood analysis (ie, hematology and biochemistry)^h^		✓		✓	✓	✓	✓	
Echocardiographic assessment^i^		✓		✓	✓	✓^e^	✓	
ECG^j^ assessment		✓		✓	✓	✓^e^	✓	
Plasma troponin I level assessment	✓^k^	✓^k^		✓	✓	✓	✓	
Mammography (if the patient did not undergo mastectomy)		✓					✓	
Plasma BNP^l^ assessment		✓		✓	✓	✓	✓	
Plasma myeloperoxidase and high-sensitivity CRP^m^ assessment (if available)		✓		✓	✓	✓	✓	
Inclusion and exclusion criteria checklist	✓							
Blood sample for genetic analysis		✓						
Plasma sample for micro-RNA analysis		✓						✓
Stool sample		✓						✓
Oncological treatment (plan and changes) and cycle			✓	✓	✓	✓	✓	✓
Information on treatment status (ongoing or completed)				✓	✓	✓	✓	
Concomitant medications	✓	✓	✓	✓	✓	✓^e^	✓	✓
GSRS^n^		✓						✓
Patient lifestyle questionnaire		✓						✓
Verification of completion of self-administered scales and questionnaires (ePsycHeart section)^o^		✓	✓	✓	✓	✓	✓	
Cognitive effect assessment (if the center has specialized personnel)		✓			✓		✓	
Verification of collection of data from wearable devices				✓	✓			
Collection of information on patient’s out-of-pocket expenses					✓		✓	
Hand grip test		✓			✓		✓	
AE^p^ assessment		✓	✓	✓	✓	✓	✓	✓

^a^May be 1 or 2 visits.

^b^At the first visit after the end of each treatment, which should be within 14 to 25 days. The time of these sample collections will vary in relation to the therapeutic schedule of the patient.

^c^ICF: informed consent form.

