#### The CARDIOCARE Mobile App

The CARDIOCARE mobile app is installed on the Motorola smartphone provided to patients, which they will have to return after use (end of month 6—T3). The CARDIOCARE app allows access to 2 different settings containing specific modules (described in this section) depending on the group—standard practice or enhanced behavioral and psychological monitoring—the patient is assigned to.

The Cognitive Stimulation, Education and Training, Vision and Hearing, and Psychology and Well-being (except for the Questionnaires submodule) modules will only be accessed by the intervention arm of the study.

The six modules are (1) Mobility and Vitality, (2) Cognitive Stimulation, (3) Education and Training, (4) Geriatric Syndrome Assessment, (5) Vision and Hearing, and (6) Psychology and Well-being.

The Mobility and Vitality module contains 4 submodules, which are the nutrition questionnaire, physical activity, the cardio recording session, and the hand grip session. Together, these submodules will provide a collection of graphs—such as bar and pie charts—representing data on the patient’s overall functional well-being, sleep duration, physical activities, and average HR, as well as proxies of the patient’s stress levels.

The Cognitive Stimulation module includes 4 cognitive games, which are Find the Word, tic tac toe, Color Beans, and Drawing. If played consistently, such games can foster the patient’s attention, concentration, and working memory capacities, thereby counteracting the cognitive impairment often found in patients undergoing oncological treatments [21].

The Education and Training module includes 2 submodules. The first one is Breast Cancer Material, which contains patient-oriented information related to breast cancer and cardiotoxicity and on the potential psychological and social implications that breast cancer and its treatment can have. This submodule provides a deeper awareness about the clinical implications of the disease and guidance for the patients to preserve their psychological well-being. The second submodule is named Training and contains a video tutorial for patients to improve their balance and reinforce their muscle strength.

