The Geriatric Syndrome Assessment module includes 2 submodules. The first one is Incontinence Management, which will allow each patient to report urination incidents, perform guided exercises for pelvic floor strengthening, and set reminders for toilet use. The second one is the Fall Mitigation submodule, where the patient can access the Otago program, a set of exercises designed to help them enhance and restore their balance [22].

The Vision and Hearing module includes the Vision Test and Hearing Test submodules. The first is an assessment of the patient’s vision capacity that was designed based on the Snellen test guidelines. The second one is an assessment of the patient’s hearing capability designed based on the whisper test guidelines.

Finally, the Psychology and Well-being module includes behavioral and psychological interventions corresponding to 5 submodules: expressive writing, BPS, ABCDE (A=activating event or situation; B=beliefs; C=consequences; D=disputation of beliefs; E=effective new approach), Biofeedback Session, and Questionnaires. The interventions in the first 4 modules aim to mitigate the psychological risk factors associated with cardiotoxicity development and deterioration of the patient’s QoL. The fifth submodule, Questionnaires, includes 15 self-reported measures that will provide critical information on the patient’s levels of perceived stress, resilience, anxiety and depression, self-management and emotion regulation capacity, coping skills, perceived social support, satisfaction with life, QoL, and levels of optimism (see Table 3 for the list of questionnaires used).

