### Statistical Procedure

#### Overview

The CARDIOCARE study proposes a comprehensive approach to measure the efficacy of the eHealth intervention by assessing its impact on 2 primary outcomes: intrinsic capacity and QoL in older patients with breast cancer. A prospective, multicentric study with 750 patients aged ≥60 years assigned to standard practice or enhanced behavioral and psychological monitoring groups will be conducted.

The enhanced behavioral and psychological monitoring group receives access to the eHealth psychological, behavioral, and functional modules on the CARDIOCARE mobile app. The primary measurements are intrinsic capacity, evaluated using physiological, physical, and cognitive parameters through wearable devices (Garmin Venu SQ watch and Polar H10 sensor) for the first 6 months, and QoL, measured through self-reported questionnaires integrated into the CARDIOCARE app covering aspects such as stress, resilience, and emotional regulation. Multimodal data, including clinical (cardiac imaging and biochemical markers), psychological (anxiety and depression scales), and behavioral data are analyzed to obtain a holistic understanding of the patient. The data are collected at baseline (T0) and every 3 months up to 12 months (T5).

This longitudinal approach captures changes over time. The intervention group undergoes targeted psychological, behavioral, and functional eHealth interventions. The comparison between the intervention and control groups will provide useful information on the interventions’ impact on mitigating cardiotoxicity and improving QoL.

As of October 17, 2024, a total of 375 patients have been enrolled in the clinical study. For all these patients, data of different categories are collected and used in the training of the risk stratification model of cardiotoxicity and the prediction model of QoL. Once the model validation phase is complete, the results will be made available and presented in a subsequent publication.

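### Sensory ability is listed as an intrinsic-capacity end point, but the only vision and hearing tests described are closed to the control arm

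*Protocol article*

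**What the plan says.** All references are to the protocol article.

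- **End point.** Objectives and Rationale states that "Psychological and behavioral variables will also be measured as secondary end points". It then sets out how intrinsic capacity is evaluated, with the numbered item "2) sensory ability (Snellen test and whisper test") placed between mobility and vitality.
- **Where the tests are.** Novelty and Study Aim says "Sensory screening is also conducted in the eHealtHeart main modules" and describes a Snellen-type vision test and a whisper-type hearing test on the phone, each repeatable without limit within a day. The CARDIOCARE Mobile App section says "The Vision and Hearing module includes the Vision Test and Hearing Test submodules". Table 1, which lists eHealtHeart interventions, times both tests "At baseline and at month 6".
- **Who can use them.** The same app section restricts access: "Vision and Hearing, and Psychology and Well-being (except for the Questionnaires submodule) modules will only be accessed by the intervention arm of the study".
- **Common schedule.** Of the procedures in Tables 2 and 3, Study Time Points and Procedures says "These procedures are the same for both the standard practice and enhanced monitoring groups". Neither table contains a vision or hearing test.
- **Intended comparison.** Study Design says that the phone, app and wearables given to both arms supply intrinsic-capacity indicators. It also says that restricting eHealtHeart to one arm will allow its effect on intrinsic capacity to be evaluated.

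**The concern.** An outcome can be compared between randomised arms only if it is measured in both, in the same way and at the same times. Here the measuring instrument is bundled with the intervention. The access rule shows that the authors saw this problem for the questionnaires, because it exempts that one submodule so that controls can be assessed. The Vision and Hearing module has no such exemption, although its content is testing rather than treatment.

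At stake is one listed component of a secondary end point. If the text is followed literally, the control values are absent by design. Neither imputation nor modelling can supply them, because no control patient provides any information about them.

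**Working it through.** No calculation decides this point. The check follows the end point to its instrument, then to access, then to any alternative source of data.

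1. **End point to instrument.** Objectives and Rationale names the Snellen and whisper tests. The only such tests described anywhere in the article are the app's Vision Test and Hearing Test.
2. **Instrument to module.** Both belong to the Vision and Hearing module, and Novelty and Study Aim places the sensory tests within eHealtHeart.
3. **Module to arm.** The app section limits the module to the intervention arm. Study Design limits the eHealtHeart interventions in the same way.
4. **Other sources for controls.** Table 2 lists a hand grip test and a cognitive assessment for both arms, but no vision or hearing test. Table 3 lists self-administered scales, none of them sensory. Instruments and Measures says that both groups complete an initial evaluation on the app, but does not say what it contains. It could at most yield a baseline value, and the module restriction still applies.
5. **Count under the described procedures.** Planned allocation is 375 + 375 = 750.

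| Time point | Intervention arm, planned | Control arm, described |
|---|---|---|
| Baseline | 375 | none clearly described (unspecified app evaluation only) |
| Month 6 | 375 | 0 of 375 |

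With no control value at month 6, neither a raw nor a baseline-adjusted difference in sensory ability can be estimated.

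6. **What can still be recovered.** The Results section reports 375 of 750 patients enrolled by October 17, 2024. Assuming 1:1 allocation held, about 375 / 2 ≈ 188 controls had been enrolled by that date, and about 375 − 188 = 187 were still to come. Only controls who enter after a change can have both a baseline and a month 6 value. The figure of 187 is therefore an upper limit as of that date, before dropout, and it falls as recruitment proceeds.

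**The case against.** The strongest reply is that silence in a condensed article does not prove that controls are untested. Objectives and Rationale evaluates intrinsic capacity through a comprehensive geriatric assessment that includes performance tests, and it names the Snellen and whisper tests rather than the app module. The app versions are said to be designed from those tests' guidelines, so clinic versions could exist as well. Table 2 is a summary and also omits gait speed, balance and the Geriatric 8, which are listed in the same place. The full protocol, which is not shown, might contain a sensory test for everyone.

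This limits the claim to what the article describes, but does not remove the conflict. The finding does not rest on Table 2 alone: the article contains an explicit rule that withholds the only described tests from controls. If a clinic test exists, the article still needs to say so.

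A reader might infer more, and the document does not support it:

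- **Loss of a primary outcome.** The statistical Overview speaks of "assessing its impact on 2 primary outcomes: intrinsic capacity and QoL in older patients with breast cancer", but there it characterises intrinsic capacity by physiological, physical and cognitive parameters, with no sensory part.
- **An uncomputable composite.** No intrinsic-capacity score is defined.
- **A failed analysis of covariance.** The sentence planning that analysis follows one about imaging and biomarker variables. Sensory scores are not named.
- **A biased risk model.** The variables listed for identifying predictive factors are imaging, blood, omics and microbiome measures. Vision and hearing are not among them.

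It is also fair to say that Table 1 labels these tests as screening and that no listed module aims to improve sight or hearing. The comparison that is lost is therefore a modest one.

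**Conclusion.** The inconsistency is real and of moderate severity. Under the procedures in this article, sensory ability cannot be compared between arms: controls have no described measurement at month 6, and none clearly described at baseline. The conclusion assumes that the access rule is applied as written and that no sensory test outside the app is given to controls. An unshown full protocol could overturn the second assumption.

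The effect is confined to this one component of a secondary end point. The cardiotoxicity end point, its sample size and the questionnaires, which remain open to both arms, are unaffected.

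**What to change.** Reconcile Objectives and Rationale, Study Design and The CARDIOCARE Mobile App.

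- **Preferred.** Open the Vision Test and Hearing Test submodules to both arms as assessments at baseline and month 6, and add them to Table 2. Specify that the first result at each time point is analysed, because unlimited repeats would otherwise allow practice or selection of the best score. Controls already past baseline will have no baseline value. Limit the baseline-adjusted comparison to patients in both arms who enter after the change, and report the number.
- **If a test outside the app already covers both arms.** Name it, give its time points in Table 2, and use that result in both arms instead of the app result.
- **If neither applies.** State that sensory ability is descriptive in the intervention arm only, and remove it from the between-arm end points.

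The preferred change costs an app permission setting, a line in the schedule and the associated protocol amendment. Controls already hold the phone and app until month 6. One drawback is that controls would see a screening score, which the display could hide. The last option costs only wording, but gives up the comparison.

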#### Wearable Devices

The CARDIOCARE mobile app, described previously, will process data derived from 2 technologically advanced wearable devices: the Garmin Venu SQ watch and the Polar H10 sensor. The Garmin Venu SQ watch will collect data on the patient’s HR (resting and high), body battery (percentage and charged or drained), stress (rest, low, medium, and high), intensity minutes (per week, for the current day, and goal), steps (for the current day and goal), calories (total for the current day, resting, and active), and respiration (breaths per minute, sleep average, and waking average). The Polar H10 sensor is a chest strap measuring highly detailed and accurate information about the patient’s HR and electrocardiogram.

The patient is required to wear the Garmin Venu SQ watch for the first 6 months of the study and to wear the Polar H10 sensor for approximately 30 minutes every 2 weeks. At the end of month 6 of the study (T3), each patient must return the 2 wearable devices and the smartphone to their clinical center.

Patients will also be asked to use the hand grip dynamometer at T1 and T3 to assess their hand grip strength during their cardiological or oncological visit.

### Statistical Procedure

#### Overview

The CARDIOCARE study proposes a comprehensive approach to measure the efficacy of the eHealth intervention by assessing its impact on 2 primary outcomes: intrinsic capacity and QoL in older patients with breast cancer. A prospective, multicentric study with 750 patients aged ≥60 years assigned to standard practice or enhanced behavioral and psychological monitoring groups will be conducted.

The enhanced behavioral and psychological monitoring group receives access to the eHealth psychological, behavioral, and functional modules on the CARDIOCARE mobile app. The primary measurements are intrinsic capacity, evaluated using physiological, physical, and cognitive parameters through wearable devices (Garmin Venu SQ watch and Polar H10 sensor) for the first 6 months, and QoL, measured through self-reported questionnaires integrated into the CARDIOCARE app covering aspects such as stress, resilience, and emotional regulation. Multimodal data, including clinical (cardiac imaging and biochemical markers), psychological (anxiety and depression scales), and behavioral data are analyzed to obtain a holistic understanding of the patient. The data are collected at baseline (T0) and every 3 months up to 12 months (T5).

This longitudinal approach captures changes over time. The intervention group undergoes targeted psychological, behavioral, and functional eHealth interventions. The comparison between the intervention and control groups will provide useful information on the interventions’ impact on mitigating cardiotoxicity and improving QoL.

As of October 17, 2024, a total of 375 patients have been enrolled in the clinical study. For all these patients, data of different categories are collected and used in the training of the risk stratification model of cardiotoxicity and the prediction model of QoL. Once the model validation phase is complete, the results will be made available and presented in a subsequent publication.

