### Objectives and Rationale

The objectives and rationale of this prospective clinical study are as follows:

To stratify patients aged ≥60 years with breast cancer based on their risk of developing cardiotoxicity. The rationale is that, so far, multiple studies have explored the effects of specific risk factors; however, these studies have yet to deal comprehensively with the impact of clinical, biological, psychological, and behavioral risk factors and their interactions.To evaluate the effects of eHealth psychological and behavioral interventions on the intrinsic capacity and QoL of older patients with breast cancer and on their risk of developing cardiac toxicity. The rationale is that, although recent studies associate psychosocial and behavioral characteristics with the risk of developing cardiovascular diseases, these studies on older patients with breast cancer are still limited [16]. However, gaining such knowledge is necessary to generate hypotheses on using eHealth interventions to support this clinical population.

The primary study end point is to evaluate and monitor the onset of cardiotoxicity, where subclinical cardiotoxicity is defined as preserved left ventricular ejection fraction (LVEF; ie, LVEF≥50%) with >15% reduction in global longitudinal strain relative to the baseline or new rise in cardiac troponin I or natriuretic peptide levels in plasma and clinical cardiotoxicity is defined as the reduction in LVEF by ≥10% from baseline to a value of <50% at any time point during study follow-up [17,18].

Secondary end points include intrapatient assessment of major adverse cardiovascular events (MACEs) [19,20] (angina pectoris, acute myocardial infarction, major ventricular arrhythmias, pacemaker implantation, acute heart failure [New York Heart Association class 4], acute ischemic brain disease with neurological persistence evidence, and severe hypertension requiring treatment with angiotensin-converting enzyme or β-blockers), intrapatient assessment of plasma troponin I levels during the follow-up and their association or agreement with LVEF, intrapatient assessment of plasma brain natriuretic peptide elevation, hospital admissions due to cardiovascular causes or falls, cardiovascular death, noncardiovascular death, and health-related QoL (assessed using the European Organisation for Research and Treatment of Cancer Quality of Life Questionnaire–Breast Cancer, a validated breast cancer patient-reported outcome measure).

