#### Statistical Considerations Regarding the Design

The primary statistical analysis will use an intention-to-treat approach. Therefore, all patients involved in the study will be included in the final analysis. Results will be presented using descriptive statistics (mean, SD, median, and range for continuous variables and proportions for nominal variables). Patient baseline characteristics will be compared using a 2-sample *t* test or a nonparametric test for continuous variables, and the Pearson chi-square test will be used for qualitative variables. All statistical analyses will be conducted using 2-tailed tests and adopting a 5% significance level. The effect of the interventions on the primary end point will be analyzed using the Cox proportional hazards model. Point estimates and 95% CIs will be calculated for the hazard ratio of the standard practice group versus the enhanced behavioral and psychological monitoring group. Any statistically significant difference between the 2 groups at baseline will be balanced by the multivariable adjustment. A logistic regression or Cox proportional hazards model will also be used to evaluate the effect of the interventions on the secondary end points in the 2 groups. Continuous variables such as those obtained from imaging and biochemical and molecular biomarkers will be summarized descriptively at baseline and follow-up visits. The differences between the 2 groups during the different follow-up visits will be evaluated using the analysis of covariance considering the corresponding baseline measurement as a covariant.

Finally, for the cost-effectiveness analysis, the health and QoL outcomes observed during the study will be used to calculate the QALYs. These QALYs will be combined with cost data in a cost-utility analysis to estimate the cost per QALYs associated with the implementation of the CARDIOCARE model and the eHealtHeart interventions. The incremental cost-effectiveness ratio will also be calculated to evaluate the CARDIOCARE model’s effectiveness compared to current care practices. Therefore, the incremental cost-effectiveness ratio, which will be calculated using a threshold approach, will allow us to better understand how to distribute and allocate the different health care resources.

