#### Sample Size Considerations

To identify the adequate sample size for the CARDIOCARE prospective study, a power analysis was conducted with 2-tailed α=.05 and 1 – β=.80. On the basis of this, and considering the 21% incidence of cardiotoxicity in our target population and the expected 10% dropout rate, it was estimated that a total of 736 patients (ie, 368 patients in the intervention arm and 368 patients in the control arm) would be large enough to detect a 40% relative risk reduction in the incidence of increased levels of troponin I (taken as a cardiotoxicity proxy) in this population. Such a sample size would also allow for the evaluation of the effectiveness of the behavioral and psychological interventions integrated into the study in mitigating, preventing, or delaying the onset of cardiotoxicity associated with oncological therapies for older patients with breast cancer.

The sample size calculation was followed by the Fisher exact test, conducted using the G*Power software (version 3.1.9.4). Considering our power analysis results and the number of patients affected by breast cancer each year, all clinical centers in the CARDIOCARE consortium agreed on the final recruitment goal of 750 patients (375 for the intervention arm and 375 for the control arm).

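### Cardiotoxicity is primary in one section and intrinsic capacity and QoL in another, and the stated 80% power is for raised troponin I alone

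*Protocol article*

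**What the plan says.** All references are to the protocol article.

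- **Objectives and Rationale, primary.** "The primary study end point is to evaluate and monitor the onset of cardiotoxicity". Subclinical cardiotoxicity requires preserved LVEF with a fall in global longitudinal strain, "or new rise in cardiac troponin I or natriuretic peptide levels in plasma". Clinical cardiotoxicity is a defined fall in LVEF.
- **Objectives and Rationale, secondary.** Health-related QoL is in the secondary list. "Psychological and behavioral variables will also be measured as secondary end points", and intrinsic capacity comes under that sentence. Troponin also appears in the secondary list, as "intrapatient assessment of plasma troponin I levels during the follow-up and their association or agreement with LVEF".
- **Statistical Procedure, Overview.** The intervention's efficacy is measured by "assessing its impact on 2 primary outcomes: intrinsic capacity and QoL in older patients with breast cancer". The next paragraph again calls these two the primary measurements.
- **Statistical Considerations Regarding the Design.** "The effect of the interventions on the primary end point will be analyzed using the Cox proportional hazards model", with a hazard ratio and 95% CI. "All statistical analyses will be conducted using 2-tailed tests and adopting a 5% significance level". Secondary end points get a logistic or Cox model. Continuous variables, with imaging and biomarkers as the examples, get an analysis of covariance with the baseline value as covariate.
- **Sample Size Considerations.** With two-sided alpha 0.05, power 0.80, a 21% incidence of cardiotoxicity and 10% dropout, 736 patients are needed to detect a "40% relative risk reduction in the incidence of increased levels of troponin I (taken as a cardiotoxicity proxy"). The recruitment goal was then set at 750.
- **Results.** The paragraph on protocol version 1.2 says that identification of cardiotoxicity now also includes MACEs. The Objectives section lists MACEs as a secondary end point.

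**The concern.** Two sections of the same document give different answers to the question of which result decides the trial. The Overview uses the primary label twice, and its choice matches the first aim in the Abstract, so it cannot safely be put down to a slip of the pen. As the text stands, a favourable QoL or intrinsic capacity result could be reported as a primary result on the strength of the Overview even if cardiotoxicity showed no difference. A favourable cardiotoxicity result could equally be reported as primary on the strength of the Objectives. Every test is at 5%, and nothing says how the level is shared if more than one outcome is primary.

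The power statement has a related gap. Its base rate is labelled cardiotoxicity, its effect is labelled troponin I, and its test is a comparison of two proportions, whereas the primary analysis is a Cox model of the full end point. A reader cannot tell what power the trial has for the end point that the Objectives section names.

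**Working it through.** **1. Which outcome is primary**

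| Section | Cardiotoxicity onset | Intrinsic capacity, QoL | Troponin I |
|---|---|---|---|
| Objectives and Rationale | primary | secondary | component of the primary; levels also secondary |
| Overview | effect to be compared, not labelled primary | the two primary outcomes | not named |
| Statistical Considerations | fits the Cox model | do not fit the Cox model | not named |
| Sample Size | source of the 21% | no power given | variable that is powered |

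The Overview contradicts the Objectives section directly. The Cox analysis, which refers to one primary end point in the singular, agrees with the Objectives section.

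**2. Error rate if the labels were used as they stand**

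For k independent tests at 5%, the chance of at least one false positive is 1 − 0.95^k.

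- k = 2: 1 − 0.9025 = 9.75%.
- k = 3 (cardiotoxicity, intrinsic capacity, QoL): 1 − 0.857375 = 14.3%.

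Positive correlation between the outcomes would lower these figures.

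**3. Reproducing the sample size**

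Inputs from Sample Size Considerations: control rate 0.21; 40% relative reduction, so 0.21 × 0.6 = 0.126; two-sided alpha 0.05; Fisher exact test; dropout 10%. Allocation is 1:1 (Study Design).

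Exact power by full enumeration is 0.7996 at 330 per arm and 0.801 at 331 per arm. Then 331 / 0.9 = 367.8, rounded up to 368 per arm, or 736 in total. This matches the stated figure, so the arithmetic is sound.

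**4. Power for the full end point**

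This needs the rate of the full end point and the effect on it, and the document does not give these explicitly. All results below are for a two-sided Fisher exact test with 331 evaluable per arm.

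*Reading A: 21% is the rate of the full end point and the 40% reduction applies to it.* Power is 0.801.

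*Reading B: 21% is the troponin rate and the composite rate is higher.* Assumptions, not in the document: composite control rate C of 0.30, 0.35 or 0.40, and troponin independent of the other components. The rate of the other components is then o = 1 − (1 − C)/0.79. If only troponin falls by 40%, the treated rate is 1 − (1 − 0.126)(1 − o).

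| C | o | Treated rate, only troponin falls | Power | Treated rate, composite falls by 40% | Power |
|---|---|---|---|---|---|
| 0.30 | 0.114 | 0.226 | 0.553 | 0.180 | 0.945 |
| 0.35 | 0.177 | 0.281 | 0.449 | 0.210 | 0.977 |
| 0.40 | 0.241 | 0.336 | 0.366 | 0.240 | 0.992 |

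If each component separately falls by 40%, the treated rate is 1 − (1 − 0.126)(1 − 0.6o), that is 0.186, 0.219 and 0.252. Power is then slightly lower, at 0.92, 0.96 and 0.98.

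These figures are for a comparison of proportions, as in the document's own calculation, and not for the Cox model.

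**The case against.** The best defence is that the Overview is an outlier. The Objectives section, the Cox analysis and the sample size all centre on cardiotoxicity, and one Cox analysis of one end point at two-sided 5% is specified. Much of this stands, and it rules out several stronger readings.

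- **Three primary outcomes.** A reader might count troponin I as a third. The document never calls it primary. It is a proxy used for sizing, a component of the primary definition and a secondary end point. Two competing primary definitions are stated, not three.
- **No confirmatory test.** A reader might infer that none exists. The Cox analysis is one, and it can only fit cardiotoxicity. The fault is that the Overview points elsewhere.
- **The 80% power is wrong.** The document labels its 21% as the incidence of cardiotoxicity. If the 40% reduction also refers to the full definition, 80% carries over unchanged. The low values under Reading B rest on assumptions that the document does not make.
- **No suitable model for continuous scores.** The analysis of covariance is offered for continuous variables with imaging and biomarkers as examples, so QoL and intrinsic capacity scores are not excluded. The text is only unclear on which model they get.

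The document also nowhere says that success on any one outcome is enough, so 14.3% is what the labels would permit and not a stated decision rule. None of this removes the contradiction between the Overview and the Objectives section.

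**Conclusion.** The point holds in two parts.

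First, the document states two incompatible primary definitions. This follows from the text alone and needs no assumption. It matters because it changes which result the trial may present as its main finding, and it has to be corrected. The 14.3% applies only if three independent outcomes could each be claimed at 5%.

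Second, the power is correctly calculated but is stated for raised troponin I, with a base rate carrying a different label. Whether the primary end point has 80% power cannot be determined from the document: it is 0.80 under Reading A and between 0.37 and 0.99 under the assumed variants of Reading B. The direction is open, so this is a gap in the justification and not evidence that the trial is too small.

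**What to change.** 1. **Overview:** name cardiotoxicity onset as the single primary end point, tested at two-sided 5%, and relabel intrinsic capacity and QoL as secondary.
2. **Objectives and Rationale, and Results:** reconcile whether MACEs are part of the cardiotoxicity definition or a secondary end point only.
3. **Statistical Considerations Regarding the Design:** state that continuous QoL and intrinsic capacity scores are analysed with adjustment for the baseline value, by the analysis of covariance already given or a mixed model, and not by logistic or Cox models.
4. **Sample Size Considerations:** say whether the 21% and the 40% refer to troponin I or to the full end point, and restate the power for the primary end point on that basis.

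The cost is wording in the protocol and analysis plan, plus one short power calculation. No change to recruitment or data collection follows from it. The restated power may be less favourable than 80%. The changes should be made before any comparison between the arms is seen; the article reports 375 of 750 patients recruited by 17 October 2024.
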